#### a) Interactions

These include errors in which interacting drugs are prescribed, and these interactions can vary between minor and major. Four standard levels are described- severe, in which harm is likely; moderate, in which harm may occur in some situations, but it is reasonable for the physician to prescribe the drug provided that special monitoring or other interventions are simultaneously indicated; potential drug interactions in which an interaction is theoretically possible, but unlikely or likely but of trivial importance; and extremely rare potential interaction. All of the above will be counted in the data analysis.

#### b) Dosing and route of administration errors

These are errors in which the prescribed dose or route of administration are incompatible with the recommended guidelines for that patient, based on weight, concurrent drugs or illnesses, and age.

#### c) Legibility

These are errors in which the writing on the prescription is not easily legible, in the pharmacist's opinion.

### Sample size and analysis plan

The unit of analysis for this trial is the individual prescription, adjusting for clustering of patients within physicians. Given an estimated intra-class correlation value of 0.05, a minimum of 65 weeks of prescribing is required to have 80% power for a two sided test to detect an absolute decrease of 5% from with a control baseline error rate of 25% with a type I error of 5%.

Descriptive statistics will be calculated for all variables of interest. Continuous measures will be summarized using means and standard deviations whereas categorical measures will be summarized using counts and percentages. The principal outcome measure, total prescribing error using PDA-generated versus written prescriptions, will be assessed using a two sample, two-sided test of proportions. This analysis will be performed on an intention-to-treat basis. All analyses will be carried out using the SAS Version 9.1 statistical program (SAS Institute, Cary, NC, USA).

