### Study population

This trial has been conducted within ambulatory outpatient clinics at an academic health sciences centre in Toronto, Ontario, Canada (August 2005 – October 2006). Both a specialist setting (Rheumatology, Dermatology and Cardiology patients) and a primary care Family Medicine setting were used. There are approximately 40 full-time physicians within these clinics, who see a total of approximately 1000 patients each week.

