### Study design

The study was a 65-week, cluster randomized (3:1 allocation ratio), parallel study with time as the element of randomization. The randomization scheme was computer generated by the biostatistics department at the hospital. The unit of allocation and randomization was the 'week'; although the unit of analysis is the prescription, with adjustment for clustering of patients within physicians. All participating physicians were trained to use electronic prescribing software, but only half of the weeks in the study period were allocated as intervention or "on" weeks, during which the software was switched on, and prescribing was carried out electronically.

Physician training consisted of a simple two hour training course and follow-up tutoring where necessary. The Health Informatician on the project used regular check-ins and a help-line pager to ensure that all technical issues were fixed in a timely manner and that any prevalent user errors with regard to the software were addressed. No further training was conducted in order simulate real-world conditions with limited user support.

During control periods all prescriptions were written on paper as per standard practice. During intervention periods or "on" weeks, all prescriptions were to be filled using the PDAs and the electronic prescribing software. The randomization was employed by turning the prescribing software servers in each clinic on and off according to the randomization scheme. A health informatics assistant was responsible for carrying out the randomization and the allocation was kept concealed until midnight on the last day of the previous week. If a physician tried to enter a prescription on his or her handheld on a control or "off" week, the system immediately gave a message that the wireless network was not been detected, and that the software was inaccessible.

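### The stated 80% power at 65 weeks is out of reach if the ICC of 0.05 applies to the randomised week; if it applies to physicians, correlation within the week was left out

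*Protocol article*

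**What the plan says.** All references are to the Methods of the protocol article.

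- **Study design** fixes the randomised unit: "The unit of allocation and randomization was the 'week". It describes a 65-week "cluster randomized (3:1 allocation ratio), parallel study", and later in the same paragraph says that "only half of the weeks in the study period were allocated as intervention or 'on' weeks". The allocation is therefore given both as 3:1 and as 1:1, and for 3:1 the larger arm is not named.
- **Sample size and analysis plan** opens with "The unit of analysis for this trial is the individual prescription, adjusting for clustering of patients within physicians". The next sentence begins "Given an estimated intra-class correlation value of 0.05" and continues that "a minimum of 65 weeks of prescribing is required to have 80% power". The target is a 5-point absolute fall from a 25% control error rate, with a two-sided test at 5%. The level to which the ICC belongs is not named.
- **Study population** gives about 40 physicians, "who see a total of approximately 1000 patients each week". The number of prescriptions per week behind the calculation is not given.

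**The concern.** When whole weeks are switched on or off, the precision of the comparison depends on the number of weeks and on how strongly prescriptions in the same week resemble each other. More prescriptions per week help only up to a limit of 1/ICC effective prescriptions per week. At an ICC of 0.05 that limit is 20, which is small against the size of trial needed to separate 25% from 20%. The only clustering named near the power statement is within physicians, which is not the unit that was randomised.

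This is the article's only power claim. A null result would be read against it, as 80%-powered evidence that a 5-point reduction is absent. If the true power is well below 80%, that reading is unsafe.

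**Working it through.** **Inputs.** From Sample size and analysis plan: p1 = 0.25, p2 = 0.20, two-sided alpha 0.05, power 0.80, ICC = 0.05, two-sample test of proportions. From Study design: 65 weeks in total, week as cluster, allocation 1:1 or 3:1. Assumed: m analysable prescriptions per week. The 1000 patients a week serve as a proxy, and m is varied from 100 upwards.

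**Step 1. Effective prescriptions needed.** With f the control fraction, d = 0.05 and p̄ the weighted mean rate:

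S0 = √[p̄(1−p̄)(1/f + 1/(1−f))], S1 = √[p1(1−p1)/f + p2(1−p2)/(1−f)], N = (1.96·S0 + 0.8416·S1)²/d² (pooled). The unpooled form replaces S0 by S1.

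At 1:1, S0 = 0.8352 and S1 = 0.8337, so N = (1.6370 + 0.7016)²/0.0025 ≈ 2188, or 1094 per arm. At 3:1 the pooled totals are 2868 (three on-weeks per off-week) and 2960 (the reverse). The unpooled totals are 3024 and 2794.

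**Step 2. Attempt to reproduce 65 weeks.** Weeks needed = N·[1+(m−1)·0.05]/m. At m = 1000 the design effect is 50.95 and 1:1 needs 2187.5 × 50.95/1000 = 111.5 weeks. As m grows without limit the requirement falls only to 2187.5 × 0.05 = 109.4. The figure of 65 is not reproduced as a total.

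**Step 3. What 65 weeks supply.** Effective N = 65m/[1+(m−1)·0.05]:

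- m = 100: 6500/5.95 = 1092
- m = 1000: 65,000/50.95 = 1276
- no limit on m: 65/0.05 = 1300

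**Step 4. Power at 65 weeks.** Power = Φ[(d√N − 1.96·S0)/S1]. At the ceiling with 1:1: (0.05·√1300 − 1.6370)/0.8337 = 0.199, giving 57.9%.

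| m per week | 1:1 | 3:1 (both directions, pooled and unpooled) |
|---|---|---|
| 100 | 51% | 39–42% |
| 1000 | 57% | 44–47% |
| ceiling | 58% | 45–48% |

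With the pooled test at m = 1000, three on-weeks per off-week gives 47.3% and the reverse 44.1%. With unpooled variance the order swaps (44.4% and 47.3%). A t-test on 63 df with whole weeks gives about 56% at 1:1 and 43–46% at 3:1.

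**Step 5. What would be needed, at m = 1000 and ICC 0.05.**

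- Weeks for 80% power: 111–112 at 1:1. At 3:1, 146 or 151 pooled and 154 or 142 unpooled, so about 142–154.
- Difference detectable with 80% power in 65 weeks (solving step 4 for p2): about 6.5 points at 1:1 and 7.2–7.6 points at 3:1.

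**Step 6. Week-level ICC at which 80% would hold.** ICC = (65m/N − 1)/(m − 1). At m = 1000 and 1:1: (65,000/2187.5 − 1)/999 = 0.0287. At 3:1 the range is 0.0205–0.0223. At m = 100 the limits fall to 0.020 (1:1) and 0.012–0.013 (3:1).

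**Step 7. Other clusters at ICC 0.05.**

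- Four clinics with separate schedules give 260 clinic-weeks. At 1:1 each must supply 2187.5/260 = 8.41 effective prescriptions, so m = 8.41 × 0.95/(1 − 0.05 × 8.41) ≈ 14 per clinic-week gives 80%. At 3:1 about 22–26 are needed. At 250 per clinic-week, power is 94–99%.
- Physician-weeks of 1000/40 = 25 prescriptions have a design effect of 2.2, so 2188 × 2.2/1000 ≈ 5 weeks would do. For 65 weeks to be the minimum at 1:1, volume would have to be near 2188/65 ≈ 34 prescriptions a week, about one per physician-week.

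**The case against.** The strongest reply is that 0.05 was never meant as a week-level ICC. It follows directly on a sentence about patients within physicians, and the Discussion says that physicians act as their own controls. Each physician then contributes to both arms, and the design effect for parallel clusters does not apply to a physician ICC. Read as week-level, 0.05 also implies a standard deviation of √(0.05 × 0.25 × 0.75) ≈ 9.7 points in the weekly error rate among the same 40 or so physicians. That is a large value to attribute to the plan's authors. This stands: the level is not stated, and the low power figures hold only if it is the week.

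It does not rescue the 80%. A calculation resting on a physician ICC alone assumes in effect that weeks do not differ, although weeks are what was randomised.

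A second reply is that other clusterings cannot be dismissed by counting 1000 patients as 1000 analysable prescriptions. Outcome data come from pharmacy callbacks and from the hospital pharmacy's forms, so the analysable volume may be much smaller. This also stands. A reader might infer that no reading gives 80% at 65 weeks, but with 260 clinic-weeks about 14 prescriptions each would do so at 1:1. Study design mentions servers in each clinic, yet it describes a single scheme with the week as the unit, so the clinic-week reading is possible rather than stated.

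A reader might also infer that a per-arm count was taken for the total, since 1094 × 5.95/100 = 65.1 weeks per arm when m = 100. The article gives no such m, so this remains conjecture.

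**Conclusion.** The power statement does not follow from the design and inputs given with it. If 0.05 is the correlation within the randomised week, 80% is unattainable with 65 weeks in total. The ceiling is about 58% at 1:1 and 45–48% at 3:1, whatever the volume, and lower with fewer prescriptions. If 0.05 is a physician-level ICC, the within-week correlation has been left out. The 80% then depends on an unstated week-level ICC of no more than about 0.029 (1:1) or 0.021–0.022 (3:1) at 1000 prescriptions a week, and less at smaller volumes.

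A reader might go further and conclude that the trial had roughly a coin-flip chance of detecting a 5-point reduction. The article does not support that as a fact, because it does not say to which level 0.05 belongs. What is established is the ceiling on the week-level reading and the gap on the physician-level reading. Both rest on one common schedule of 65 weeks, the usual design effect with equal cluster sizes, and no credit for other sources of precision.

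**What to change.** Rewrite the power sentence so that the cluster is the randomised week, or the clinic-week if clinics had separate schedules. State the level of the 0.05. Use a week-level ICC, the expected analysable prescriptions per cluster (not patients seen) and the single allocation ratio actually used, and say whether 65 is the total or a per-arm count.

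Replace the 80% with the power that results, or with the difference detectable at 80%. If 0.05 proves to be the week-level ICC, the restated power is at most about 58% (1:1) or 45–48% (3:1). The detectable difference at 1000 prescriptions a week is then about 6.5 or 7.2–7.6 points. If 0.05 is the physician-level ICC, those figures should not be used. Give a separate week-level value and show power over a plausible range.

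The cost is a recalculation and a reworded paragraph, with no extra weeks or patients. The stated power may become less favourable.

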### Outcomes

The principle outcome measure was total prescribing error, as measured by the number of call backs received from pharmacists to prescribing physicians offices. These are defined as potential medication errors picked up by the pharmacist at the time the prescription is filled. Rates will be compared between intervention and control weeks. Prescribing errors can take many forms and are of different levels of severity and a single prescription can have several errors and all will be counted. The denominator for total error is the total number of prescriptions and the numerator is the sum of the following types of error:

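### The primary comparison is worded by prescription mode but labelled intention-to-treat; it should be fixed as weeks randomised on versus weeks randomised off

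*Protocol article*

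**What the plan says.** Under Sample size and analysis plan, the Protocol article describes the principal outcome as "total prescribing error using PDA-generated versus written prescriptions", tested with a two-group test of proportions. The following sentence reads "This analysis will be performed on an intention-to-treat basis".

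Under Outcomes, the comparison is put differently: "Rates will be compared between intervention and control weeks".

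Under Study design, the week is the unit that was randomised. For off weeks, "During control periods all prescriptions were written on paper as per standard practice", and the software could not be reached if a physician tried it. For on weeks, "all prescriptions were to be filled using the PDAs and the electronic prescribing software". This is an instruction; no block on paper is described.

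The same section gives the share of on weeks in two ways, "cluster randomized (3:1 allocation ratio), parallel study with time as the element of randomization" and "only half of the weeks in the study period were allocated as intervention". That is a separate conflict. It matters here only because the on-week share enters the calculation.

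**The concern.** The article gives two rules for placing a prescription in an arm. Under Outcomes, a paper prescription written in an on week belongs to the intervention arm. Under the literal wording of the analysis plan, it belongs to the written group, together with all off-week prescriptions. Two analysts, each following one section, would put the same prescription in opposite arms.

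Randomisation of weeks makes on-week and off-week prescriptions comparable. It does nothing for the choice between PDA and paper within an on week, which the physician makes or circumstances force. If that choice is related to the risk of error, a comparison by mode mixes the effect of the software with the effect of selection. Crossover can run only one way, from on weeks to paper, because the software was inaccessible in off weeks. The Discussion relies on randomisation to limit bias, and a comparison by mode would give that up for the primary result.

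**Working it through.** **Figures from the article.** The control error rate is 25% and the target is an absolute decrease of 5 points (Sample size and analysis plan). The article gives no figure for the effect of grouping by mode, so there is none to reproduce. The 65-week sample size plays no part in this point.

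**Quantities the article does not give (assumptions below).**
- c: share of on-week prescriptions made on the PDA.
- s: share of all prescriptions that fall in on weeks. With equal volume per week, s is 50% if half the weeks are on. Under 3:1 it is 75% or 25%, because the article does not say which way the ratio runs.
- d: error rate of on-week paper prescriptions minus that of PDA prescriptions, arising from selection alone.

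**Formula with no true effect.** On-week and off-week error rates are both p = 25%.
- PDA rate = p − (1−c)d.
- On-week paper rate = p + cd.
- Rate in the pooled written group = [s(1−c)(p + cd) + (1−s)p] / [s(1−c) + (1−s)] = p + sc(1−c)d / (1−cs).
- Written minus PDA = (1−c)d + sc(1−c)d / (1−cs) = **d(1−c) / (1−cs)**.
- Grouped by allocated week, the difference is 25% − 25% = 0.

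**Illustration at c = 80%.**
- On-week paper error 30%: PDA rate = (0.25 − 0.2×0.30)/0.8 = 23.75%, so d = 6.25 points and d(1−c) = 1.25.
- On-week paper error 40%: PDA rate = (0.25 − 0.2×0.40)/0.8 = 21.25%, so d = 18.75 points and d(1−c) = 3.75.
- The divisor 1−cs is 0.8, 0.6 and 0.4 at s = 25%, 50% and 75%.

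| On-week paper error | s = 25% | s = 50% | s = 75% |
|---|---|---|---|
| 30% | 1.6 points | 2.1 points | 3.1 points |
| 40% | 4.7 points | 6.3 points | 9.4 points |

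Direct check of one cell (40%, s = 50%): written group = (0.5×0.25 + 0.1×0.40)/0.6 = 27.5%, and 27.5 − 21.25 = 6.25 points.

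**Selection gap needed for a false 5-point difference**, d = 5(1−cs)/(1−c):

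| Uptake c | s = 50% | s = 75% |
|---|---|---|
| 50% | 7.5 points | 6.25 points |
| 70% | 10.8 points | 7.9 points |
| 80% | 15.0 points | 10.0 points |
| 90% | 27.5 points | 16.25 points |

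At c = 100% the false difference is zero and the two groupings coincide. If d is negative, so that the riskier prescriptions go to the PDA, every difference changes sign and counts against the software.

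**The case against.** The strongest reply is that the phrase is only shorthand for the arms. Study design describes off weeks as paper and on weeks as PDA, so naming the arms by mode is natural. The intention-to-treat sentence follows at once, and Outcomes states the comparison by week. On that view most of the text already points to week-based grouping and one phrase is loose. This is a fair reading. A reader might infer that an as-treated primary analysis was settled; the article does not show that.

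Two further inferences also go too far. The first is that the bias must favour the software. That requires on-week paper prescriptions to be the riskier ones, and the article says nothing about which prescriptions went to paper. Physicians could equally have kept the PDA for complicated orders, since it checks each order against guidelines and a dosing and interactions database. The second is that the false effect would exceed the 5-point target. It does so under some inputs and not others, as the tables show, and neither uptake nor the selection gap is reported. The training, regular check-ins and help line described under Study design could have kept uptake high.

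What remains is the conflict itself. If the phrase is shorthand, the primary comparison is still written in two ways that assign on-week paper prescriptions to different arms. The sentence defining the primary test is the one an analyst would follow. This is not detail that an article can leave to a fuller document, because both statements are made here and they disagree.

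**Conclusion.** The point holds as a contradiction in how the primary comparison is defined. The literal wording groups by mode, while the intention-to-treat sentence and the Outcomes section group by allocated week. They agree only at full on-week uptake, which is instructed but not enforced.

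If the literal wording were followed, the comparison would lose the protection of the week randomisation. The direction of the bias is unknown. With no true effect, 25% error in both kinds of week and an assumed 80% uptake, its size is 1.6 to 3.1 points when on-week paper prescriptions carry 30% error and 4.7 to 9.4 points when they carry 40%, for on-week shares from 25% to 75%. So it can range from negligible to larger than the 5-point target. The uptake, the 30% and 40% rates and the on-week shares are all assumptions chosen to show the range, not estimates for this trial.

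**What to change.** In Sample size and analysis plan, define the primary comparison as all prescriptions written in weeks randomised on versus all prescriptions written in weeks randomised off, whatever mode was actually used. Remove the mode-based description from the primary analysis. If PDA versus written prescriptions is also to be compared, label it as a secondary, as-treated analysis.

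The cost is one sentence. It needs no change to the design and agrees with the Outcomes section and the intention-to-treat statement.

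The downside is dilution. If the software lowers error by 5 points only on prescriptions actually made with it, and by the same amount on each, the week-based difference is 5c: 4.5 points at 90% uptake, 3.5 at 70% and 2.5 at 50%. That is the effect of making the system available, which is what a pragmatic trial randomised by week estimates.

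### The named primary test has no clustering term, and no stated adjustment covers the week, which is the unit that was randomised

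*Protocol article*

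**What the plan says.** The Study design section of the protocol article states "The unit of allocation and randomization was the 'week"', and continues "although the unit of analysis is the prescription, with adjustment for clustering of patients within physicians". The Abstract (Methods) says the same of practitioners.

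Sample size and analysis plan opens with "The unit of analysis for this trial is the individual prescription, adjusting for clustering of patients within physicians". It then sizes the trial with an ICC of 0.05 and concludes that "a minimum of 65 weeks of prescribing is required to have 80% power for a two sided test", where the target is a fall from 25% to 20% at a 5% type I error. Its next paragraph gives the primary analysis: total prescribing error, PDA-generated against written prescriptions, "will be assessed using a two sample, two-sided test of proportions".

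No section names a method that carries out the promised adjustment, and none mentions an adjustment for week.

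**The concern.** There are two separate problems.

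First, a two-sample test of proportions, taken as named, computes its standard error as if prescriptions were independent. The same section says they are not, and uses an ICC to size the trial.

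Second, the promised adjustment is for physicians, but physicians were not randomised. All prescriptions in a week share one allocation. Anything common to that week, such as staffing, technical trouble or the pharmacies' readiness to call back, falls wholly on one side of the comparison. A physician term does not absorb variation that all physicians share in a given week.

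Only about 65 units were randomised. If the roughly 1000 patients seen each week yielded one analysed prescription each (an assumption), the test would count 65 × 1000 = 65,000 independent observations. A significant primary result could then reflect week-to-week variation rather than the software.

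**Working it through.** **Inputs from the article.** 65 weeks; 25% against 20%; two-sided alpha 0.05; power 80%; ICC 0.05, level not stated; about 40 physicians and about 1000 patients per week (Study population); physicians act as their own controls (Discussion).

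**Assumed, because not stated.** Analysed prescriptions per week, m = 25, 100 or 1000; week-level ICC of 0.001, 0.01 or 0.05; one on/off schedule for all clinics.

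**Step 1. Can the 65 weeks show which level the ICC refers to?**
Without clustering, n per arm = [1.96·√(2 × 0.225 × 0.775) + 0.842·√(0.25 × 0.75 + 0.20 × 0.80)]² / 0.05² = 1094, or 2188 in total at 1:1.
- Week as cluster, design effect DE = 1 + (m − 1) × 0.05. At m = 100, DE = 5.95 and 1094 × 5.95 / 100 = 65.1 weeks *per arm*, about 130 in total. As m grows, the total falls only to 2188 × 0.05 = 109.4. So 65 weeks in total is not reached at any m.
- Physician as cluster, crossed with on and off weeks: the variance factor is 1 − 0.05 = 0.95, and 2188 × 0.95 / 65 = 32 prescriptions per week would give 65 weeks.

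The figure is compatible with different readings under different unstated inputs. It does not settle the level of the ICC.

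**Step 2. Correlation within week.**
True type I error of the plain test = 2·[1 − Φ(1.96 / √DE)], with DE = 1 + (m − 1) × ICC.
Example, ICC 0.05 and m = 100: 1.96 / √5.95 = 0.80, giving 0.42.

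| Week-level ICC | m = 25 | m = 100 | m = 1000 |
|---|---|---|---|
| 0.001 | DE 1.02; 0.05 | DE 1.10; 0.06 | DE 2.00; 0.17 |
| 0.01 | DE 1.24; 0.08 | DE 1.99; 0.17 | DE 10.99; 0.55 |
| 0.05 | DE 2.20; 0.19 | DE 5.95; 0.42 | DE 50.95; 0.78 |

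**Step 3. Correlation only within physician (ICC 0.05).**
If each physician is equally present in on and off weeks, the physician effect cancels from the difference and DE = 0.95. Then 1.96 / √0.95 = 2.01, giving 0.044, which is slightly conservative.

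**Step 4. Simulation check.**
65 weeks, 40 physicians, ICC 0.05, 4000 replicates per scenario, at 120 and 1000 prescriptions per week. The Study design section gives both a 3:1 ratio and half the weeks on, so each scenario was run at 1:1 and with 49 of 65 weeks on.

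| Where the correlation lies | Type I error |
|---|---|
| Physician only, balanced attendance | 0.043 to 0.051 |
| Physician only, each present in 70% of weeks (assumed) | 0.05 to 0.09 |
| Physician-week | 0.06 to 0.20 |
| Week, 120 per week | 0.45 to 0.46 |
| Week, 1000 per week | 0.78 to 0.79 |

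The allocation ratio makes little difference. The level of the correlation and the weekly volume decide the result.

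**The case against.** The strongest reply has three parts.

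1. A comparison of two proportions can itself be adjusted for clustering, for example by a design-effect correction or a Rao-Scott chi-square. The article promises adjustment three times and carries an ICC into its sizing. Read together, the sentences may mean an adjusted test, with the procedure left to a fuller document. This stands in part. A reader might infer that the two statements are irreconcilable, or that the investigators chose to ignore clustering; the article supports neither. It supports an inconsistency that must be resolved. The reply does not reach the second problem, because the adjustment promised, however carried out, is for physicians and not for the randomised week.

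2. Under the only clustering the plan names, physicians cross over between on and off weeks, so the plain test is close to nominal. This stands, and it rules out any statement that p-values would necessarily be too small. It depends on negligible correlation within week and within physician-week and on even attendance, none of which the article states or justifies.

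3. The large figures need both a week-level ICC and a high volume. This stands. The sentence before the ICC concerns physicians, and the article counts patients seen, not prescriptions analysed. Errors were captured from call-back forms and forms from the hospital's internal pharmacy, so the analysed volume could be well below 1000 per week.

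**Conclusion.** The point holds in a conditional form. The named primary test has no clustering term and is inconsistent with the plan's own adjustment and ICC. No stated adjustment covers the week, so the gap remains even if the physician adjustment is made. This goes beyond condensed detail: the article names the primary test and names the wrong level for the adjustment.

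The consequence is a range. Type I error at nominal 5% runs from about 0.04 to 0.05 (physician-only correlation, balanced attendance) to 0.78 (week-level ICC 0.05, 1000 prescriptions per week). The intermediate cases depend on the assumed volume and ICC. A reader might take 0.78 as the trial's actual error rate. The article does not support that, since it states neither of the two inputs behind it. The inconsistency and the omission of week are certain; the size of the inflation is not.

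**What to change.** Replace the plain test of proportions as the primary analysis with one of these:

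- a prescription-level regression that accounts for both randomised week and physician, by random effects or cluster-robust variance; or
- a week-level comparison, with one error rate per week and on and off weeks compared by a weighted t-test or by re-randomising the week schedule under the procedure actually used.

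Report the on-minus-off difference with its cluster-adjusted 95% CI. If the ratio was 3:1, the smaller arm has only about 65 / 4 ≈ 16 weeks, so a regression should use a small-sample correction. State which level the ICC of 0.05 refers to and how many prescriptions per week were assumed.

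The cost is a change of wording and a few more lines of analysis code, with no new data and no change to conduct. The confidence interval will be wider where week-level correlation exists, and little is lost where it does not. If 0.05 is a week-level ICC, a valid analysis of 65 weeks at 1:1 has power of about 0.51 at 100 prescriptions per week and 0.57 at 1000, so the 80% claim would also need to be revisited.

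### Weeks are randomised, but the primary test treats prescriptions as the independent units, so error-rate changes shared within a week get no variance and type I error can exceed 5%

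*Protocol article*

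**What the plan says.** Study design describes a "parallel study with time as the element of randomization", with the week as the unit of allocation. On how the weeks were allocated it says only this: "The randomization scheme was computer generated by the biostatistics department at the hospital". It mentions neither blocking nor stratification over calendar time.

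Sample size and analysis plan then names the primary test, which "will be assessed using a two sample, two-sided test of proportions". The only adjustment stated is for physicians: "The unit of analysis for this trial is the individual prescription, adjusting for clustering of patients within physicians". The Abstract and Study design name the same adjustment. No section gives the week a place in the analysis, whether as a cluster, a random effect or a covariate.

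**The concern.** When a whole week is switched on or off, anything that moves the error rate for all prescriptions in that week moves with the allocation. The study ran from August 2005 to October 2006. Season, staff changes and habits in recording callbacks or completing forms could each shift the recorded rate across all physicians at once. Letting physicians serve as their own controls, as the Discussion intends, removes differences between physicians but not changes they share.

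With 65 randomised units, on and off weeks will usually differ somewhat in mean calendar position, and in any random week effects. A prescription-level test takes its standard error from the number of prescriptions, so it reads such differences as signal. At stake is whether the primary p-value and confidence interval mean what they claim.

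**Working it through.** **Inputs from the article:** 65 weeks; control error rate 25%; ICC 0.05 (cluster level not stated); about 1000 patients a week. **Assumed, because the article gives no figure:** linear drift of 0, 5 or 10 percentage points over the study; 200, 400 or 1000 prescriptions a week; unrestricted allocation.

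**1. The plan's own figure.** The article states no number for this point. The nearest is 65 weeks for 25% versus 20%. Without clustering, n per arm = [1.96√(2×0.225×0.775) + 0.8416√(0.1875+0.16)]²/0.05² = 1094. With weeks of m prescriptions as clusters, the weeks needed are 2×1094×[1+0.05(m−1)]/m. This falls towards 2×1094×0.05 = 109 as m grows and never reaches 65. The 65-week figure therefore does not show that week-level variation was allowed for.

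**2. Chance imbalance in calendar position.** The variance of 65 consecutive weeks is 65×66/12 = 357.5. The SD of the difference in mean week is √[357.5(1/n₁+1/n₂)]: 4.69 weeks for 32/33, and 5.44 for 49/16.

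**3. Resulting spurious difference.** SD × drift/64. For 32/33 this is 0.37 points (5-point drift) or 0.73 points (10-point drift). For 49/16 it is 0.43 or 0.85. Its mean over randomisations is zero.

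**4. Standard error of the stated test (32/33).** √[0.1875(1/n₁+1/n₂)/m] = 0.76, 0.54 and 0.34 points at m = 200, 400 and 1000.

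**5. Type I error.** 2[1−Φ(1.96·SE/√(SE²+SD²))], with simulation (2000 runs per cell, half the weeks on) in brackets:

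| Prescriptions a week | No drift | 5 points | 10 points |
|---|---|---|---|
| 200 | 5% (5.0%) | 7.8% (8.2%) | 15.8% (16.2%) |
| 400 | 5% (4.2%) | 10.5% (11.1%) | 24.7% (25.4%) |
| 1000 | 5% (5.2%) | 18.3% (18.6%) | 41.0% (40.6%) |

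**6. Allocation ratio.** SE and SD both scale with √(1/n₁+1/n₂), so their ratio does not depend on the split. Simulation at 3:1 agrees: 8%, 11% and 20% at 5 points; 16%, 24% and 41% at 10 points.

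**7. Adjustment for physician.** Testing within-physician on/off differences at a 10-point drift, half the weeks on, still gave 16%, 24% and 39%.

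**8. Random week variation, no trend.** If the ICC of 0.05 applied to weeks, the week variance would be 0.05×0.1875 = 0.009375. The spurious difference would then have SD √[0.009375(1/32+1/33)] = 2.4 points. The simulated type I error of the prescription-level test was 55%, 65% and 79%.

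**9. What restores 5%.** A linear time term in the prescription-level test gave 4.6% to 5.8% in the cells with a trend only. Under step 8 it left 55%, 65% and 80%. A week-level analysis without any time term held about 5% in both settings (4.2% to 5.8% with a trend, 4.6% to 5.6% under step 8).

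**10. Blocking over calendar time.** With blocks of 4 and a 10-point drift, the stated test gave 5.6% in simulation. What remains comes mainly from the 65th week, left over after 16 blocks. It shifts its arm's mean by about 32.5/33 = 0.98 weeks, or 0.98×10/64 = 0.15 points. Against the SEs in step 4, that implies roughly 5% to 7%.

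**The case against.** **Time covariates are usually left to the analysis plan.** This is fair, and a missing season or spline term would be no finding by itself. But the article names the primary test and the unit it counts. That is a stated rule, not an omission.

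**The missing time term is not the cause.** This stands. A reader might infer that adding calendar time would repair the test. Step 9 shows that it is neither necessary (week-level inference holds about 5% without it) nor sufficient (55% to 80% rejection with random week variation). The fault is that the week is ignored as the randomised unit.

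**The magnitudes rest on assumptions.** This also stands. No drift is given, and 1000 patients a week is clinic traffic, not a count of prescriptions with usable error data. At 32 prescriptions a week (a volume not in the article), the SE is 1.90 points and the formula in step 5 gives only about 5% and 7%.

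**Allocation may have been blocked.** The article does not say so, but computer generation does not exclude it. Blocking would nearly remove the trend problem.

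**Growing skill with the device is not a shared trend.** This stands. A reader might take the training description, including "No further training was conducted", as evidence of drift. The software was inaccessible in off weeks, so learning would act mainly in on weeks. That is a treatment effect changing over time, not a trend under the null, and it does not support the figures in step 5.

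**Conclusion.** The point holds as a mismatch between what is randomised and what the primary test counts. Its consequence is false precision and inflated type I error. A reader might infer systematic bias from the calendar imbalance. That does not follow, because the spurious difference averages zero over randomisations. Even at an assumed 10-point drift, 95% of unrestricted schemes would give no more than 1.4 points (half on) or 1.7 points (3:1), against a 5-point target.

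Under unrestricted allocation, type I error runs from about 8% (5-point drift, 200 prescriptions a week) to 41% (10-point drift, 1000 a week). It stays at 5% if there is no trend and no other week-to-week variation, and close to 5% under a trend alone with time-blocked allocation. None of these is an estimate of this trial's actual error rate, since drift, volume and allocation method are not stated. The direction of the fault does not depend on them: any positive week-level variation that the allocation scheme does not balance makes the stated test too liberal. The change should be made.

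**What to change.** Replace the two-sample test of proportions with an analysis whose inference is at the level of the randomised week. Three routes would serve:

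- a model for week or clinic-week error rates;
- a prescription-level model with a week random effect;
- a re-randomisation test that follows the actual allocation scheme.

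Keep physician or clinic effects, and add a prespecified calendar-time term (for example linear plus season, or a low-order spline) to remove avoidable noise. State whether allocation was blocked over time, and make the analysis respect it. In the blocked simulation with a trend, a plain week-level comparison that ignored the blocks almost never rejected (0.0%), while adding the time term gave 4.5%.

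Forms were collected weekly and allocation is by week, so calendar week should be available without new data. The cost is analysis wording, a few degrees of freedom out of 65 and probably a wider confidence interval.

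Separately, Study design gives a 3:1 ratio but also says "only half of the weeks in the study period were allocated as intervention". The two must be reconciled, although the type I error figures here are much the same under either.
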